### Implementation and data management

A Trial Management Committee (TMC), including chief investigators from each site, clinical research associates (CRA), the ethics committee and institutional review board, and treatment representatives, is established to ensure a proper implementation throughout the trial process. The chief investigators will be responsible for ensuring adherence to the study protocol, compliance with the consent process, follow-up, and accurate data collection. The trial coordinating center, authorized by TMC, will report all the enrollment records and schemes every month and will monitor the recruitment phase and assess the trial progresses in collaboration with the clinical investigators. A research summary conference will be held every 6 months to evaluate progresses and discuss possible solutions to the problems that may arise.

All data will be collected and recorded using CRFs and the EDC; a data management committee (DMC, located at Clinical Research Institute, Shanghai Jiaotong University School of Medicine) will be established to develop and maintain the EDC and supervise the data quality. Monitoring and auditing will be performed against the original documentation on a monthly basis by the CRA of DMC. Regular visits will be scheduled in each participating center to ensure the compliance with the research program requirements. In case of anomalies, the CRA will promptly submit the information to the investigators in order to find a solution.

All investigators participating in this study will comply with the requirements of the Data Protection Act 1998 concerning the collection, storage, processing, and disclosure of personal information. Access to collated participant data will be restricted to approved individuals involved in the treatment process and representatives from regulatory authorities. Computers used to input data will set up user names and passwords with limited access measures. Published results will not contain any personal data that could allow the participants’ identification. All study documents will be kept for a minimum of 5 years, and documents will not be destroyed without permission from the leading research center when the minimum retention period has elapsed.

### Data analysis

Patient characteristics and variations in both treatments and outcomes will be defined using descriptive statistics. Continuous variables will be described as mean and standard deviation (SD) or as median and interquartile range (IQR). To assess the differences between cohorts, appropriate tests will be performed according to the distribution and scale of measurement. Student’s t-tests or Mann-Whitney U tests will be used for continuous variables, and *X*^*2*^ tests or Fisher’s exact test will be used for categorical variables. Exploratory analyses on AEDH will be performed, aiming at understanding the complexity of the disease and to discover new possible associations. In addition to standard descriptive statistics, multivariable regression models or other analyses may be used if appropriate. *P* < 0.05 will be considered to be statistically significant. Factors such as age, the severity of injury, and the timing of injury will be included as covariates in the primary analysis, with the center considered as a random effect.

More specifically, the outcome measures will be assessed using the GOSE, an ordinal scale. The GOSE categories of death, vegetative state, lower severe disability, and upper severe disability will be considered as unfavorable outcomes. Favorable outcomes will be defined by following the GOSE categories: lower moderate disability, upper moderate disability, lower good recovery, and upper good recovery. However, GOSE conventional analysis usually dichotomizes the ordinal scale into a binary scale, and this may discard a lot of relevant information, reducing both the outcomes’ clinical relevance and the statistical efficiency of the analysis. Ordinal logistic regression analysis will be used to quantify the prognostic effects across the full range of the GOSE. And the final effect will be a pooled estimate of the common odds ratio. Additionally, a secondary analysis will be reported for the two pre-specified binary outcomes: dead versus alive and unfavorable versus favorable outcomes.

So far, there is no reliable data able to clarify the potential selection bias caused by the number of patients who, after initial allocation to a craniotomy, eventually require a DC. This study aims to be a pragmatic trial to improve and specify the surgical options for AEDH. Data of patients who, after initially undergoing craniotomy, eventually require a DC will be recorded, as the incidence of additional craniocerebral surgery after the initial surgical treatment (secondary endpoint). All these information will help in evaluating the potential selection bias.

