Ordinary surgical strategy principally aims to quickly reduce ICP and promote the repositioning of the brain herniation, if concurrent [3]. The Brain Trauma Foundation (BTF) has produced an informative guideline on the surgical indications for AEDH, but no specific surgical options. Although craniotomy for AEDH is conventionally employed in practice, some patients suffered from clinical deterioration by secondary injuries, including fatal cerebral infarction (CI), especially in cases combined with preoperative herniation [3]. In such cases, an initial hematoma evacuation with additional decompressive craniectomy (DC) might effectively prevent and/or alleviate postoperative CI. However, the relatively low incidence of postoperative CI has led few surgeons to opt for the removal of the bone flap in patients with AEDH. In addition, the lack of high-quality evidence regarding the use of decompressive craniectomy in AEDH has determined a great variability in terms of practices between hospitals, countries, and even among surgeons within the same hospital. Other critical issues, such as the proper identification of subgroups that may not benefit from DC, are in need of further exploration. To date, there are no clinical trials that have investigated the validity of decompressive craniectomy in AEDH patients with herniation.

In this research, called Prospective Randomized Evaluation of Decompressive Ipsilateral Craniectomy for Traumatic Acute Epidural Hematoma (PREDICT-AEDH), we present a study protocol for a randomized controlled trial. Our aim is to compare the outcome and cost-effectiveness of DC versus craniotomy in the treatment of TBI patients with cerebral herniation undergoing acute epidural hematoma evacuation.

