### Sample size calculation, randomization, and blinding

Our data and results from a previous retrospective study are showing that almost all the patients who received a synchronous DC (93%) had a GOSE of 6.63 ± 1.27, with a favorable outcome (defined by the GOSE categories: lower moderate disability, upper moderate disability, lower good recovery, and upper good recovery). Patients who received craniotomy had a GOSE of 5.78 ± 1.58, with a favorable outcome in 72% of the patients [6]. We calculated the sample required in this clinical trial with a significance level of 5% (two-sided) and a power of 80% to demonstrate the difference in the rate of favorable outcome, with an assumption that 10% of the patients would be lost during follow-up. Ultimately, considering the quality of the study, the sample size is enlarged to 120.

All participating centers must have a neurosurgical on-call team and an emergency department responsible for the admission of head-injured patients to identify eligible patients. After recording the patient’s clinical information, including Glasgow Coma Scale (GCS), pupillary reactivity, and CT findings, an electronic data collection (EDC) database will generate the subject identification number that will be allocated to the eligible patients. A secure central web-based randomization management information system will be used for the randomization of eligible patients. The system will provide an immediate allocation along with the patient randomization record number for the trial, and individual randomization record numbers can be checked at any time. Blocked randomization will be used, with a block size of 4 and an allocation ratio of 1:1. The 24-h central web-based randomization management information system will be backed by one delegated person (available 24 h per day) who will assure the cover-up of the record allocation. The delegated person responsible for randomization will not be involved in the treatment procedure. A confirmatory email will be sent to the investigator of each center involved to verify the allocation.

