### Treatment interventions

The randomization process allocates eligible patients to one of the two surgical treatment groups. Surgical options, according to the guidelines for the surgical management of AEDH [7], consist of the evacuation of the hematoma with a craniotomy, or with additional DC, leaving a large bone flap [3]. However, the bone flap must be replaced and secured with a fixation system (plates and screws) in patients who received a craniotomy. It is essential that all treatments for surgical management of AEDH are consistent within the two groups, including preoperative preparation and anesthesia. The only difference between the two arms will be represented by the removal or replacement of the bone flap. To provide well-established surgical techniques and a standardized surgical treatment is the essential aim of this study. The operation will be performed by a qualified senior neurosurgeon within each of the participating centers.

The post-operation management process and the medical decisions concerning the patients will not be affected by their recruitment into the PREDICT study. All patients will receive postoperative care management according to the guidelines and intensive care protocols, including radiographic or biochemical examination. Normally, a cranioplasty is recommended to reconstruct the skull in patients who underwent DC. The treatment in case of complications will differ considerably between patients, according to their clinical manifestations (epilepsy or cerebral infarction, or late complications as hydrocephalus).

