There is a considerable controversy regarding the initial neurosurgical management of AEDH [4, 12, 13]. In some cases, neurosurgeons are confronted with the decision to evacuate the hematoma with or without a DC, especially in patients with brain herniation [6, 14]. The BTF recommends that all patients with an EDH volume of more than 30 cm^3^ should undergo surgical evacuation of hematoma, regardless of Glasgow Coma Scale [3]. Although no sufficient data are available to support certain surgical treatment methods, craniotomy provides a more complete evacuation of the hematoma [3]. However, evidence is showing that a set of patients experienced clinical deterioration after the initial hematoma-evacuation craniotomy, as a result of secondary brain injuries with increased ICP [10, 15–18]. Additionally, the incidence of post-traumatic cerebral infarction secondary to AEDH is reported to be 18.2% and even higher among patients with high-risk factors, e.g., transtemporal location, preoperative shock for longer than 30 min, bilateral mydriasis, preoperative brain herniation, and so on [3, 6, 19]. Nevertheless, decompressive craniectomy has displayed a potential in controlling raised ICP and is recommended as soon as possible in case of serious post-traumatic cerebral infarction secondary to AEDH [6, 10, 15, 17–19]. DC seems to represent the best surgical option in some cases of AEDH. However, previous evidence from clinical practice indicates that bone flap removal is not always essential in patients with EDH [5, 20]. DC performed inappropriately with initial hematoma-evacuation might lead to unavoidable complications, such as abnormal hemodynamics, subsequent cerebral necrosis, and infarction, as well as a need for cranioplasty [15, 21]. Inappropriate management with undefined surgical indications can lead to unnecessary death and disability, which may defeat the target of “toward zero mortality” while managing AEDH. To date, no consensus has been reached around the opportunity to proceed with decompressive craniectomy in the management of AEDH with brain herniation. And also, regarding the type of surgical techniques during decompressive craniectomy, it is in need of further investigation, by mean of randomized controlled trials [10].

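### The distribution-based test rule probably sends skewed 6-month cost to a rank test, which does not compare mean cost per patient, the quantity that the economic aims need

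*Protocol article*

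**What the plan says.** The Data analysis section gives one general rule. To compare groups, "appropriate tests will be performed according to the distribution and scale of measurement", and then "t-tests or Mann-Whitney U tests will be used for continuous variables". The summary follows the same pattern: mean with SD, or median with IQR. A later sentence leaves room for more, since "multivariable regression models or other analyses may be used if appropriate", but it is optional and not tied to any endpoint.

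Aims and outcomes lists an economic evaluation among the secondary endpoints, defined as total AEDH-related medical expenses (operations, hospital stay, rehabilitation) within 6 months of injury. It is a continuous variable, and the article states no separate method for it. Background sets the purpose: "Our aim is to compare the outcome and cost-effectiveness of DC versus craniotomy". Aims and outcomes names economic benefits beside efficacy and complications.

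Two other statements bear on the shape of the costs. Treatment interventions says: "Normally, a cranioplasty is recommended to reconstruct the skull in patients who underwent DC". The sample size section plans on favourable outcome in 93% after DC and 72% after craniotomy, that is, unfavourable outcome in 7% and 28%.

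**The concern.** Which treatment costs less overall is a question about the arithmetic mean: total spend is mean cost times number of patients, and a cost-effectiveness comparison uses the difference in means. Mann-Whitney has another null hypothesis, that a randomly chosen DC patient is as likely to cost more as to cost less than a randomly chosen craniotomy patient. The two nulls coincide if the cost distributions have the same shape. They need not coincide otherwise.

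The article gives some reason to expect different shapes. Cranioplasty would add a moderate cost to many DC patients. A larger share of unfavourable courses after craniotomy could give that arm a smaller but much more expensive tail. Ranks register the widespread moderate cost and largely ignore how expensive the tail is.

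At stake is the direction of the economic conclusion. In addition, if the test is picked after looking at the distribution, the hypothesis being tested stays open until the data are seen.

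**Working it through.** **What the article supplies.** It gives no cost mean, SD, effect size or power for cost, so there is no stated figure to reproduce. Usable inputs from the sample size section are 120 patients allocated 1:1 (60 per arm), 10% loss (60 × 0.9 = 54 per arm), and unfavourable outcome in 28% v 7%.

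**What is assumed.** Cost is in units of the mean base cost.
- Craniotomy cost = B + U₀·T, with U₀ ~ Bernoulli(0.28).
- DC cost = B + U₁·T + V·c, with U₁ ~ Bernoulli(0.07) and V ~ Bernoulli(v).
- B is lognormal with mean 1 and CV 0.6. T, the extra cost of an unfavourable course, is lognormal with mean X and CV 0.6. c is the cranioplasty cost, and v is the share of DC patients who incur it within 6 months.

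Mean difference (DC − craniotomy) = v·c − (0.28 − 0.07)·X = v·c − 0.21·X.

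**Which test the rule would pick.** Under this model with v = 0.9, a Shapiro-Wilk test rejected normality in at least 97% of simulated trials. A choice made by distribution would then normally land on Mann-Whitney.

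**Equal mean costs.** Set X = v·c/0.21. For v = 0.9 and c = 0.5, X = 0.45/0.21 = 2.14. Rejection at two-sided 5%, 54 per arm, 2,000-3,000 trials per setting:

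| c | Mann-Whitney, v = 0.9 | Mann-Whitney, v = 0.5 |
|---|---|---|
| 0.1 | 5.0% | not run |
| 0.2 | 7.4% | 5.0% |
| 0.3 | 12.8% | 5.5% |
| 0.4 | 20.3% | not run |
| 0.5 | 33.6% | 8.6% |

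At v = 0.9 the Welch test stays at 4.6-5.2%. From c = 0.3 upward, at least 93% of the Mann-Whitney rejections there call DC the dearer arm. At v = 0.7, Mann-Whitney rejects in 7-17% for c = 0.3 to 0.5. The Monte Carlo standard error near 5% with 2,000 trials is √(0.05 × 0.95/2000) = 0.5 percentage points. The 5.0% and 5.5% are therefore compatible with 5%, and the 8.6% is not.

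**True mean saving with DC.** Take v = 0.9 and c = 0.25, so v·c = 0.225.
- X = 3: saving 0.63 − 0.225 = 0.405. Mann-Whitney rejects in 5.4%, Welch in 28.6%.
- X = 4: saving 0.84 − 0.225 = 0.615. Mann-Whitney rejects in 5.3%, Welch in 40.5%.

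**DC truly dearer.** Again v = 0.9.
- c = 0.3, X = 0.5: excess 0.27 − 0.105 = 0.165. Mann-Whitney rejects in about 42%, Welch in 27%.
- c = 0.5, X = 1: excess 0.45 − 0.21 = 0.24. Mann-Whitney rejects in 67%, Welch in 38%.

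**A different cost model** (also assumed; 54 per arm, 10,000 trials).
- Lognormal costs with equal means and log-SD 0.6 (DC) v 0.8 (craniotomy), 0.5 v 0.8, and 0.5 v 1.0: Mann-Whitney rejects in 17%, 32% and 66%.
- Equal means, with a large extra cost in 10%, 18% or 25% of craniotomy patients against a general upward shift for all of the DC arm: 56%, 27% and 13%. The middle share is close to the 18.2% infarction incidence cited in the Discussion.
- Welch rejects in 4.7-8.0% over these settings, so it too drifts somewhat above 5% at the most unequal skew.
- Equal medians with a DC mean 18%, 31% or 38% lower: Mann-Whitney rejects in 5-6%, Welch in 19%, 39% and 47%.
- Identical distributions: Mann-Whitney 4.8%. Pure scale factor of 1.5 at log-SD 0.8: Mann-Whitney 71%, Welch 61%.

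**The case against.** The strongest objection is that the article never assigns cost to Mann-Whitney. The rule is generic, names no normality test, and allows the t-test, which does compare means. The regression sentence could cover a model for mean cost, and a fuller economic plan may exist. A reader might infer that the protocol prescribes a rank test for cost. It does not; that is a likely consequence of the rule if cost is judged non-normal. What stands is narrower: the one rule that is stated covers this endpoint, and nothing stated exempts it. The article also does not name the mean as the target, but its aim of cost-effectiveness implies one.

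A second objection is that every cost input is assumed. The article says that cranioplasty is normally recommended, without giving uptake or timing, and costs count only to 6 months. At 50% uptake the inflation almost disappears. Giving every unfavourable outcome an extra cost is also doubtful, because that category includes deaths, and an early death may be cheap. Craniotomy patients converted to DC at the initial surgery are withdrawn, which may thin the expensive tail. These points limit the size of the error and leave the mismatch between test and aim in place.

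Third, the rank test is not worse everywhere. Where DC is truly dearer by a general shift, it has more power than Welch. That is correct, and it is a cost of the proposed change.

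**Conclusion.** The point holds in a limited form. Under the stated rule, 6-month total medical expenses would probably be compared by a test that does not address mean cost per patient, although the economic aims need the mean difference. With arms of different shape, the rank test can report a difference at equal mean cost or miss a real mean saving.

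The size cannot be fixed from the article. At 54 per arm, CV 0.6 and equal means, Mann-Whitney rejection runs from about 5% to 34% at 90% cranioplasty uptake within 6 months, and from about 5% to 9% at 50% uptake. With little uptake, a low cranioplasty cost or similar shapes, it stays near nominal.

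A reader might infer that the economic result will be wrong, or will favour craniotomy. The documents do not support that, since they contain no cost data and the error depends on how the shapes differ. Nor does the point reach the main result: cost is one of several secondary endpoints, and GOSE is analysed by ordinal logistic regression.

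**What to change.** Exempt total medical expenses from the distribution-based choice of test, in the analysis section or the SAP. Pre-specify that the arms are compared on the difference in arithmetic mean 6-month cost, whatever the skew, with a bootstrap or Welch 95% CI. A generalised linear model for the mean (for example gamma with identity or log link), with the planned covariates, is an alternative. Keep median and IQR as description only.

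This takes one sentence and no new data. The price is a wider interval that is more sensitive to a few very expensive patients, and some loss of power where the arms differ by a general shift in cost.

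### Covariate adjustment is committed only for the primary analysis; secondary endpoints and the binary GOSE outcomes have no committed adjusted method, so available precision or power may be given up

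*Protocol article*

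**What the plan says.** All the relevant statements are in the Data analysis section of the protocol article.

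- **Primary analysis.** GOSE at 6 months is analysed by an ordinal model: "Ordinal logistic regression analysis will be used to quantify the prognostic effects across the full range of the GOSE". The covariate commitment is tied to that analysis: "Factors such as age, the severity of injury, and the timing of injury will be included as covariates in the primary analysis". The same sentence adds the centre term, "with the center considered as a random effect".
- **Differences between arms in general.** Two-sample tests are named by type of variable: "t-tests or Mann-Whitney U tests will be used for continuous variables", and for categorical data chi-square or Fisher's ("exact test will be used for categorical variables"). None is tied to a named endpoint.
- **Other modelling.** "multivariable regression models or other analyses may be used if appropriate". No endpoint, covariate set or trigger is given.
- **Binary GOSE.** "a secondary analysis will be reported for the two pre-specified binary outcomes: dead versus alive and unfavorable versus favorable outcomes". Neither a test nor adjustment is specified.

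The section on sample size, randomization and blinding says that GCS, pupillary reactivity and CT findings are recorded before allocation. The Data collection section says that the timing of injury is recorded.

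**The concern.** The plan treats age, injury severity and injury timing as prognostic enough to belong in the primary model. It also justifies the ordinal analysis by the efficiency lost when GOSE is dichotomised. The same reasoning applies to the secondary endpoints, yet the only methods the article commits to for other comparisons ignore these variables.

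Two things are at stake:

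- **Efficiency.** About 54 patients per arm are expected to be evaluable, so precision on scores and power on binary endpoints are worth having, and the baseline data are already collected.
- **Discretion.** Because regression is optional and has no trigger, the choice between an adjusted and an unadjusted result could be made after the data are seen, with P < 0.05 as the criterion. This matters most for favourable versus unfavourable GOSE. The trial was sized on that outcome, and it will be read beside the adjusted common odds ratio.

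**Working it through.** **Inputs from the protocol article.** Favourable outcome 72% (craniotomy) and 93% (DC); two-sided 5% level; 80% power; 10% loss; 120 randomised 1:1. Evaluable per arm: 120 × 0.90 / 2 = 54.

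**Assumed, because the document gives no value.** R² of the covariates for a score, 0.05 to 0.30; log-odds of a prognostic score for a binary outcome, 0.8 to 1.6 per SD.

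**The plan's own figure.** The pooled two-proportion formula is n = [1.96·√(2p̄(1−p̄)) + 0.842·√(p₁(1−p₁)+p₂(1−p₂))]² / (p₁−p₂)².

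- With p̄ = 0.825, 2p̄(1−p̄) = 0.28875, and 0.72·0.28 + 0.93·0.07 = 0.2667, this gives n = 50.2, so 51 per arm.
- Allowing for 10% loss, 51/0.9 = 56.7, so 57 per arm or 114 in total.
- The plan says it enlarged the number to 120, which is consistent with this. The sample size is not in dispute here.

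**Scores (EQ-5D-5L, MMSE).** Linear adjustment multiplies the standard error by √(1−R²). Without adjustment, the difference detectable with 80% power is (1.96 + 0.842)·√(2/54) = 0.539 SD. A comparison with 80% power unadjusted has adjusted power Φ(2.802/√(1−R²) − 1.96).

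| Assumed R² | Interval width × | Detectable difference (SD) | Power |
|---|---|---|---|
| 0 | 1.000 | 0.539 | 80.0% |
| 0.05 | 0.975 | 0.526 | 82.0% |
| 0.10 | 0.949 | 0.511 | 84.0% |
| 0.20 | 0.894 | 0.482 | 87.9% |
| 0.30 | 0.837 | 0.451 | 91.8% |

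The table ignores the degrees of freedom spent. If three covariates explain nothing, the interval widens by √(106/103) = 1.014, about 1.4%.

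**Favourable versus unfavourable GOSE, 72% v 93%, 54 per arm.**

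- Unadjusted power by formula: the critical difference is 1.96·√(0.28875/54) = 0.1433 and the standard error under the alternative is √(0.2667/54) = 0.0703. Φ((0.21 − 0.1433)/0.0703) = 82.9%.
- Simulation (3,000 trials per setting; pooled z-test against a likelihood-ratio test from logistic regression with one prognostic score) puts unadjusted power at about 85–86%. Adjusted power is about 89%, 91% and 93% at log-odds 0.8, 1.2 and 1.6. A separate run of 1,500 trials per setting gave 87–93% adjusted.
- The two tests reached different significance verdicts in about 6–10% of the simulated trials, so the choice of test can change the reported conclusion.

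For binary endpoints this gain is in power. Adjustment does not narrow the interval for an odds ratio, whose conditional and unadjusted versions are different quantities. An efficiency comparison on the interval scale needs a standardised risk difference.

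**The case against.** A reader might infer that the plan assigns every secondary endpoint to an unadjusted test. The text does not say so. The tests are listed generically, no secondary endpoint is matched to one, and the optional regression clause leaves adjustment open. A reader might also infer that the binary GOSE outcomes are to be analysed unadjusted, and so could conflict with the primary result for that reason alone. That is not supported either: no method is stated for them, they appear in the paragraph on the ordinal model, and whether the covariate sentence covers them is left unsaid. An ordinal and a dichotomised analysis can also differ for other reasons.

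It can further be argued that endpoint-by-endpoint models belong in a statistical analysis plan that is not shown, that unadjusted tests control type I error and already allow for chance imbalance, and that favourable versus unfavourable GOSE has adequate power without adjustment at the planned rates.

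Most of this stands. It removes any charge of error, bias or contradiction, and it lowers the priority. What remains is that the article is not silent: it names unadjusted tests firmly, commits adjustment for one analysis only, and leaves the rest to judgement with no rule.

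**Conclusion.** The point holds as a modest efficiency recommendation and a request to pre-specify. The plan commits adjustment for the primary analysis only. For other comparisons it firmly names only unadjusted tests, which are valid but give up precision or power that recorded baseline data could supply.

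The size rests wholly on the assumed covariate strengths. Scores gain about 2.5 to 16% in interval width (80% power becomes 82 to 92%). The binary GOSE comparison gains a few to several points of power on a base that is already adequate (about 83–86% to about 87–93%). With uninformative covariates the gain is nil and the cost about 1.4% in width. The score figures should not be carried over to length of stay or cost, which are likely to be skewed, or to endpoints with few events.

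**What to change.** Add to the Data analysis section, or to the statistical analysis plan before unblinding, that the secondary endpoints and the two binary GOSE outcomes are analysed with the same pre-randomisation covariates as the primary model:

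- EQ-5D-5L and MMSE: linear or rank ANCOVA.
- Infarction, additional surgery, SAE, dead/alive and favourable/unfavourable: logistic regression, reported with standardised risk differences.
- Length of stay and cost: an adjusted method suited to skewed data.
- Where events are few: age and GCS only.
- The two-sample tests already named: kept as sensitivity analyses.

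State also whether the random centre effect carries over to these models.

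The cost is wording and slightly more analysis work. No new data are needed, since GCS is recorded before allocation and injury timing is already collected. The one limitation is the smaller covariate set for rare events.
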